##### Endpoint

The primary endpoint will be the peak hyperaemia after the cuff release over the skin of volar aspect of forearm. In addition, area under the hyperaemic curve (AUCh), the raw value of the peak minus biological zero, increase in post-ischemic flow using area under the curve at baseline and post-ischemia will also be measured.II.Macrovascular Endothelial Function

##### Equipment and method

High-resolution ultrasonography with 2D, color, and spectral Doppler imaging with high-frequency linear-array transducer (7 to 12 MHz) and ECG gating and digital recording, an automatically deflating pneumatic blood pressure cuff and stereotactic probe-holding device. Determination of FMD of the brachial artery following release of a 250 mmHg cuff occlusion for 5 min. The post-occlusive hyperemia leads to a shear stress over endothelium and consequent nitric oxide release and dilatation.

##### Technique

Child will rest supine with arm extended in a comfortable position. Blood pressure cuff will be placed below the antecubital fossa. Optimal resting 2D longitudinal image of the brachial artery will be obtained 2 cm above the antecubital fossa and Doppler signal will be recorded with the transducer perpendicular to the vessel wall to get a double line appearance. Cuff will be inflated to 250 mmHg for 5 min followed by rapid cuff deflation. Cine 2D and Doppler images will be recorded immediately after deflation and at every 60s after deflation till a maximum of 10 min after deflation to obtain the maximum lumen diameter after cuff release. Analysis of images will be done blinded in an offline fashion with careful attention to image quality after selecting images with a clear “double-line” sign from the same time during the cardiac cycle.. Intima-lumen interfaces will be used to measure the diameter by tracing the wall. Doppler flow velocity will be measured at baseline and at each point after deflation.B.Subclinical Cardiovascular Comorbidity AssessmentsMacrovascularI.Estimation Of Carotid Intima Media Thickness (cIMT) Equipment

High resolution ultrasound scanner as for the FMD assessment with an optimal focus depth of 30–40 mm and frame rates greater than 15 Hz and automated edge detection algorithm for image processing with a 10 MHz linear array probe and a 128-radiofrequency line multi-array echo-tracking system for Quality Intima Media Thickness (RFQIMT) [Esaote BV, Maastricht, the Netherlands].

##### Method

The normal arterial wall is composed by two acoustic impedance interfaces: the transition between blood and intima, and the transition between media and adventitia. The distance between those two acoustic interfaces is the definition for IMT. Thus the cIMT will be defined by determining the thickness between the lines of Pignoli on B-mode ultrasound; with the first echogenic line representing the lumen intima interface, and the second line representing the media-adventitia interface. In addition, a high precision determination of the IMT on B mode Ultrasound with RFQIMT echo tracking will be the reference standard technique for IMT determination [This method has a minimum resolution of 21 μm with ability to measure change in diameters with 1.7-μm spatial resolution as against pure video imaging with a spatial resolution of 150 μm [22].

##### Technique

Image acquisition will be done as per standard Mannheim consensus protocol [23–25]. Briefly the child will be resting comfortably in the supine position with head turned 45° toward the side opposite the side being examined and patient’s carotid artery perpendicular to the plane of sound as much as possible. Farwall cIMT from 3 segments (distal common carotid 10 mm proximal to the carotid bulb, carotid bulb, and proximal internal carotid) will be measured at end diastole (R wave on ECG) and measurements on each side averaged to give the mean IMT for the right and left carotid arteries separately. In addition, carotid stiffness will also be assessed by using the B-mode image to place M-mode cursor across the common carotid artery 1 cm proximal to the bulb. Maximal and minimal lumen diameters from the right and left common carotid from M-mode echocardiography will be used in calculation of carotid stiffness.

##### Endpoint

The IMT from both sides will be further averaged to give the overall mean IMT. Any carotid plaque will be defined as a focal structure encroaching into the arterial lumen of at least 0.5 mm or 50% of surrounding IMT value, or an IMT value of > 1.5 mm.

##### Quality control

30 patients (15 nephrotic and 15 controls) will be revaluated and their IMT reassessed by a second ultrasonographer, in order to assess inter- and intra-observer variability to have an acceptable variation < 9%.2.MicrovascularII.Nailfold Video capillaromicroscopy Equipment & Method

Nailfold videocapillaroscope with a minimum 300X magnification with digital output [26].

##### Technique

Middle 3 mm of nailfold of ring finger of non-dominant hand will be examined using oil drop magnification.

##### Endpoint

Capillary density: Number of loops per mm Capillary dimension: The first 5 capillaries from the right hand edge of the nailfold in which arterial, apex, and venous widths could all be discerned would be chosen. Apex, arterial, venous, and total capillary width (the width at the widest point) of each capillary will be measured. Mean across 5 loops will be calculated for each of apex, arterial, venous, and total capillary widths. All loop dimensions will be log transformed to achieve normality. Architectural pattern: 6 descriptive classes: cuticilis, open, tortuous, crossed, bushy, and bizarre will be noted. Intra- and inter-observer variability/reliability of < 10% will be acceptable [27].III.Echocardiography Assessment Equipment & Method

Standard transthoracic echocardiography using 2.5–7MHZ probes equipped with tissue Doppler imaging technology as per published studies [8, 28, 29].

##### Technique

Evaluation by cardiologist blinded to the status of the subjects. All patients will undergo echocardiographic examination by a well-experienced pediatric cardiologist blinded to the diagnosis in order to reduce bias. Two dimensional images will be obtained using standard views in the left lateral decubitus position. Images will be acquired at passive end-expiration to minimize global cardiac movement from standard parasternal long axis and apical planes. Left ventricle (LV) dimensions will be obtained in the standard views. LV end systolic and end diastolic volumes will be calculated by using the modified Simpson’s method, and ejection fraction will be calculated from the LV end systole and end diastolic volumes. The left ventricular mass index (LVMI) (g/m2) will be calculated using the Devereux’s formula by the following equation: Left Ventricular Mass (LVM) = 0.80 [1.04 × (interventricular septal thickness + posterior wall thickness + end-diastolic diameter) 3 - (end-diastolic diameter) 3] + 0.6. The LVMI will be calculated as LVM divided by the body surface area (BSA). LVMI is calculated according to end-diastolic measurements of LV posterior and septal wall thickness and internal dimension, standardizing all to body surface area. Circumferential cardiac contractility and shortening will also be measured. LVMI > 38 g/Hg2.7 will be defined as LVH.

##### Quality control

Re-evaluation of 30 patients re-assessing LVMI by a second pediatric cardiologist, in order to assess inter- and intra-observer variability.IV.Flow Cytometry for Circulating Angiogenic Cells and Derivatives [30]

##### Methodology

15 ml of venous blood will be drawn into citrated and EDTA vials. The initial 5 ml will be used for biochemical testing. The subsequent 10 ml will be used for flow cytometry. Initial 3 mL of blood will not be used to avoid contamination with endothelial cells from the puncture wound of the vein. After centrifugation at 1500 rpm for 30 min at 4C, the samples will be processed further as follows.Assay of Circulating CD31+/Annexin V+ Apoptotic Microparticles

Plasma derived from 10 mL citrate-buffered blood will be immediately centrifuged at 13,000 g for 2 min to generate platelet poor plasma. Fifty microliters of platelet-poor plasma will be incubated with 4 mL of phycoerythrin (PE)-conjugated monoclonal antibody against CD31 followed by incubation with fluorescein isothiocyanate (FITC)-conjugated annexin V according to the manufacturer’s instructions. IgG FITC (Pharmingen, San Jose, California, USA) will serve as the negative control. Fluorescence-activated cell sorting (FACS) analysis will be performed immediately after staining using a FACS Calibur flow cytometer. Standard beads (Nile Red fluorescent particles, 1.7–2.2 μm, catalog number 556261, BD; Megamix 0.5–3 μm (Biocytex, France) will be used to identify microparticles in gating cells by FACS so as to standardize the set-up of MP analysis region (0.5–1 μm) and guarantee the stability of the settings. CD31+/annexin V+ microparticles will be defined as particles positively labeled for CD31 and annexin V. (CD31+/annexin V+). Data will be analyzed using Cell quest softwareb)Assay of Circulating Angiogenic Cells

A volume of 1000 microL peripheral blood will be incubated for 30 min in the dark with monoclonal antibodies against human kinase insert domain-conjugating receptor (KDR) followed by PE-conjugated secondary antibody, with the fluorescein isothiocyanate (FITC)-labeled monoclonal antibodies against human CD45, and PE-conjugated monoclonal antibody against human CD133 and with FITC-conjugated or PE-conjugated monoclonal antibodies against human CD34 and KDR. Isotype-identical antibodies will serve as controls. After incubation, cells will be lysed, washed with phosphate-buffered saline (PBS), and fixed in 2% paraformaldehyde before analysis. Each analysis will include 100,000 events. Numbers of circulating EPCs will be gated with monocytes and defined as CD34 + KDR + CD133+. For CECs, CD146 will be used.

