## Background

Nephrotic syndrome (NS) is a common pediatric renal disorder in India. With an estimated prevalence of 12–16 cases per 100,000 population and annual incidence of ~ 1.5–2 new cases per 100,000 population, at least 150,000 to 200,000 cases exist amongst Indian children and about 10,000 new cases are added every year [1, 2]. A child with NS gets exposed to multiple risk factors well known to be atherogenic and contributory to progression of chronic kidney disease (CKD) amongst adults [3, 4].

Apart from hyperlipidemia, a well-known risk factor for coronary artery disease (CAD) and a defining hallmark of NS, these children also get exposed to other risk factors associated with impaired endothelial function and adverse cardiovascular outcomes like high oxidative stress, frequent infections, sustained proteinuria, hypoalbuminemia, thromboembolism, toxicity of steroids and non-steroidal drugs like calcineurin inhibitors (hyperlipidemia,vasculotoxic and nephrotoxic effects). Many children with steroid resistant NS progress towards CKD which is known to increase cardiovascular mortality 500 to 1000 fold compared to the general population in young adults [5]. While hyperlipidemia is usually intermittent and transient in steroid sensitive nephrotic syndrome (SSNS), dyslipidemia and other abnormalities may be persistent in patients with frequent relapses (FRNS) or steroid resistant (SRNS) cases [6].

Biological plausibility of extra-renal endothelial alterations in NS arises from a longstanding recognition of increased glomerular endothelial permeability due to an ill-defined ‘permeability factor’ of extra renal origin. Mediators like platelet activating factor, VEGF family, adhesion molecules of selectin family and Nitric Oxide (NO) pathway are involved in the recruitment of inflammatory interstitial cells as well as affect endothelial cells with widespread vascular effects [1]. Occurrence of hemostatic abnormalities and generalized edema in NS attest to the wide ranging effects related to vascular endothelial dysfunction.

Very few original research studies have addressed endothelial alterations in pediatric NS. Most of the existing published data has related to uncontrolled cross-sectional studies in small number of adults with preponderance of non-minimal change disease. Broadly 3 approaches have been adopted –.

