The primary objective of this study is to define extent of endothelial dysfunction by noninvasive evaluation for impairment of macrovascular and microvascular endothelial function in children with NS versus healthy controls, by assessment of brachial artery Flow mediated dilation (FMD) and cutaneous post-occlusive reactive hyperemia (PORH), respectively. Secondary objectives includes (a) To prospectively evaluate the temporal course of progression of endothelial dysfunction over 24 months of follow-up of these children in the macrovascular and microvascular endothelium as defined by repeating brachial artery FMD and cutaneous PORH (b) To evaluate in these children the association between endothelial dysfunction and morphological markers of subclinical cardiovascular comorbidity, defined by measurement of carotid intima media thickness (cIMT) and abnormalities on Nail Fold Capillaroscopy (NFC) and echocardiography (c) To look for numerical abnormality of circulating angiogenic cells and micro-particles as a marker of endothelial dysfunction in children with NS versus healthy controls, and (d) To assess biochemical marker of endothelial dysfunction in children with NS versus healthy controls.

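### The one negative control named for the microparticle assay, a FITC-labelled IgG, matches neither the PE-labelled CD31 antibody nor the annexin V probe

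*Protocol article*

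**What the plan says.** The Methodology text of the flow cytometry section in the protocol article describes two assays.

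For apoptotic microparticles, platelet-poor plasma is stained with "phycoerythrin (PE)-conjugated monoclonal antibody against CD31 followed by incubation with fluorescein isothiocyanate (FITC)-conjugated annexin V". The event is double positive: "CD31+/annexin V+ microparticles will be defined as particles positively labeled for CD31 and annexin V". Calibration beads "will be used to identify microparticles in gating cells by FACS", which fixes a size region of 0.5–1 μm. One negative control is named: "IgG FITC (Pharmingen, San Jose, California, USA) will serve as the negative control".

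For circulating angiogenic cells, described directly afterwards, the control statement is different: "Isotype-identical antibodies will serve as controls".

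The microparticle count serves secondary objective (c), given at the end of the Background: "To look for numerical abnormality of circulating angiogenic cells and micro-particles as a marker of endothelial dysfunction in children with NS versus healthy controls".

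**The concern.** A negative control is meant to show what a stained sample looks like when the specific target is not being bound, so that the positivity threshold can be set above that background. To do this for a labelled antibody, the control should be an immunoglobulin of the same isotype with the same fluorochrome. The named control has the wrong fluorochrome for the only antibody in the assay. In the channel where its fluorochrome does fit, the probe is of a different kind.

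The endpoint is a count of events above two thresholds. If a threshold is not anchored by a suitable control, some particles may be called positive or negative wrongly. The count would then be a less valid measure of the marker that objective (c) compares between groups. The Discussion calls this flow cytometry challenging and says paediatric data are lacking, so there is little outside reference against which a misplaced gate would be noticed.

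**Working it through.** The plan gives no figure to reproduce, and the point depends on no sample size, power or alpha. The check matches each label to its control, using only the Methodology text.

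| Channel | Probe | Role in the endpoint | Negative control stated for this assay | Does it match? |
|---|---|---|---|---|
| PE | Anti-CD31 monoclonal antibody | CD31 positive | None on PE | No: the named IgG carries FITC |
| FITC | Annexin V (not an antibody) | Annexin V positive | IgG on FITC | Fluorochrome only: an IgG does not reproduce annexin V binding |

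1. **PE channel.** A tube holding FITC-labelled IgG and no PE reagent can still be read in PE, and it will show autofluorescence there. It cannot show non-specific binding of a PE-labelled immunoglobulin, and the CD31 threshold has to exclude that binding.

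2. **FITC channel.** The control shows how much FITC-labelled immunoglobulin sticks to the particles. Annexin V binds in its own way. Its background is better shown by a tube in which its binding is prevented, or by one stained with CD31-PE alone.

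3. **Size gate.** The beads standardise which particles enter the analysis by size. They say nothing about whether a particle of that size is CD31 positive, so they do not replace the missing control.

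4. **The neighbouring assay.** Isotype-identical controls are stated for angiogenic cells and not for microparticles. The article therefore does report matched controls where it plans them.

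5. **Effect on the group comparison.** Suppose the true counts are equal and misclassified events add a fraction b of the true count in both groups. The apparent ratio of nephrotic syndrome to control is then (1 + b)/(1 + b) = 1.00 for any b. A spurious group difference needs a background that differs between groups, and the documents supply no value for that. The effect on the comparison therefore cannot be quantified from them.

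**The case against.** The strongest reply is that this is a condensed article. The section cites a method source, and the annexin V step follows the manufacturer's instructions. Controls for each channel are ordinary laboratory-procedure detail, and the FITC label may be an incomplete or mistaken description of the reagent. This has weight: the absence of a PE control from the article does not prove that none is run. But the point does not rest on silence. The text goes to bench level, with conjugates, volumes, a supplier and a bead catalogue number, and it names a specific control that does not fit its own staining scheme. If the label is a slip, it still needs correcting.

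A second reply is that other safeguards limit the harm. An event must pass both criteria, so a loose CD31 gate alone adds nothing unless the particle also passes the annexin V gate. The bead set-up stabilises the settings, and the General protocols section has laboratory work done blind to clinical status. All of this stands, and it keeps the point small. It does not remove it: the second criterion is itself checked only by an IgG, and neither beads nor blinding supplies a positivity threshold.

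A reader might go further and infer that the count will be inflated in nephrotic syndrome, because the Background describes the disease this way: "Apart from hyperlipidemia, a well-known risk factor for coronary artery disease (CAD) and a defining hallmark of NS". The documents do not support that step. They nowhere say that lipid produces false CD31 events or affects this assay. The same section describes the hyperlipidaemia of steroid-sensitive disease as usually intermittent and transient, so a uniform bias across both patient groups would not follow in any case. Nor is the bead range a weakness: the 0.5–1 μm region lies within the 0.5–3 μm range of one of the bead sets, which is there to define it.

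**Conclusion.** The concern holds in a limited form. The stated negative control cannot set the CD31-PE threshold against non-specific antibody binding, and it is not a matched control for annexin V. Double-positive counts may be misclassified as a result.

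No direction or size can be given for any bias between nephrotic syndrome and healthy children. Any figure would rest on an assumed difference in background between the groups. Nor does it follow that the assay has no control at all: the size region is standardised, two criteria must be met, and the full protocol may hold further controls.

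The issue is minor. It affects one marker within secondary objective (c). The primary comparisons of FMD and PORH are unaffected, and so is the sample size, which rests on FMD and cIMT. The conclusion assumes that the article describes the staining and the control reagent as they are used.

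**What to change.** State the negative control for each label in the microparticle assay:

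- **CD31 gate:** a PE-labelled, isotype-matched IgG.
- **Annexin V gate:** a suitable annexin V negative control, for example a tube with annexin V binding prevented, or one stained with CD31-PE only.
- **Both gates:** the same controls and the same gating rule for samples from children with nephrotic syndrome and from healthy children.

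If the FITC label is an error in the article, correct it and state the annexin V control alongside.

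The cost is control reagents and extra tubes. No further blood should be needed: a stained tube uses 50 microlitres of platelet-poor plasma, so two control tubes use 2 × 50 = 100 microlitres of the plasma obtained from 10 mL of blood. Run once per batch, this is a few tubes. Run for every child, it would be 2 × 210 = 420 tubes at baseline, taking the 3 × 70 = 210 children of the Abstract. The laboratory should therefore settle the frequency in advance. Samples are analysed immediately after staining, so a control left out on the day cannot be assumed recoverable later.

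### Progenitor cells are defined by three positive markers, but the stain described uses two dyes, so the triple-positive count for secondary objective (c) cannot be obtained as written

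*Protocol article*

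**What the plan says.** The Methodology text under Flow Cytometry for Circulating Angiogenic Cells and Derivatives gives the endpoint as follows: "Numbers of circulating EPCs will be gated with monocytes and defined as CD34 + KDR + CD133", with a plus sign after the last marker as well.

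The stain is described in the same paragraph, reagent by reagent:

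- KDR, first mention: "monoclonal antibodies against human kinase insert domain-conjugating receptor (KDR) followed by PE-conjugated secondary antibody"
- CD45: "with the fluorescein isothiocyanate (FITC)-labeled monoclonal antibodies against human CD45"
- CD133: "PE-conjugated monoclonal antibody against human CD133"
- CD34, and KDR a second time: "with FITC-conjugated or PE-conjugated monoclonal antibodies against human CD34 and KDR"

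No third fluorochrome is named for this assay, and no division into tubes is given. The only gating stated is the monocyte gate. On acquisition the text says: "Each analysis will include 100,000 events".

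The count serves secondary objective (c), stated at the end of the Background: "To look for numerical abnormality of circulating angiogenic cells and micro-particles as a marker of endothelial dysfunction in children with NS versus healthy controls".

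**The concern.** A cytometer can tell two markers apart on one cell only if they carry labels it can separate. Two dyes give two readable labels, while the endpoint needs three positive markers on the same cell. If two of the three share a dye, a signal in that channel shows that one or the other is present, not both.

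The count itself is the endpoint of objective (c), because the question is whether cell numbers differ between children with nephrotic syndrome and healthy controls. The Discussion also presents the comparison of these cellular markers with the imaging markers as something not done before. If the reported number cannot correspond to the defined population, neither result can be read as the protocol intends.

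**Working it through.** **1. Plan's own figure.** There is none to reproduce. The dye assignment is a statement of method, and the 100,000 events are a setting given without derivation.

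**2. Dye assignments allowed by the text.** CD133 is fixed on PE. KDR may be on PE (secondary antibody, or the later either-dye clause) or on FITC (later clause). CD34 may be on either. That gives 2 × 2 = 4 assignments:

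| KDR | CD34 | CD133 | Defining markers that share a dye |
|---|---|---|---|
| PE | FITC | PE | KDR and CD133 |
| FITC | PE | PE | CD34 and CD133 |
| FITC | FITC | PE | KDR and CD34 |
| PE | PE | PE | all three |

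In each row at least one pair cannot be told apart. This follows from the count alone: three markers on two dyes must put two on the same dye. CD45 on FITC adds a further clash in any tube where CD34 or KDR is also on FITC.

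**3. Monocyte gate.** Gating restricts which cells are examined. It does not supply a separate label for a third defining marker.

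**4. Separate tubes.** Suppose one aliquot is stained for CD34 and KDR and another for CD34 and CD133. Scale the counts to the same volume. Let A be the number positive for CD34 and KDR, B the number positive for CD34 and CD133, and C the number positive for CD34. The triple-positive number T then satisfies only

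max(0, A + B − C) ≤ T ≤ min(A, B).

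The pairwise counts bound T but do not determine it, and whenever A + B ≤ C the lower bound is zero.

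**5. Contrast within the same section.** The microparticle assay uses two markers (CD31 and annexin V) on two dyes (PE and FITC). That definition and panel agree, so the mismatch is specific to the progenitor-cell assay.

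**6. Event number.** With N = 100,000 events and target frequency f, the expected count is N × f, the Poisson counting CV is 1/√(N × f), and the chance of no target cell is exp(−N × f). The article gives no f, so the range below is an assumption:

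| Assumed f | Expected cells | CV |
|---|---|---|
| 0.001% | 1 | 100% (37% chance of zero) |
| 0.005% | 5 | 45% |
| 0.01% | 10 | 32% |
| 0.05% | 50 | 14% |
| 0.1% | 100 | 10% |

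The events needed for a CV of 20% are 25/f: 2,500,000 at 0.001%, 250,000 at 0.01% and 25,000 at 0.1%. Whether 100,000 is enough therefore depends on a frequency the article does not state. It also depends on whether the 100,000 are all events or only those in the monocyte gate, which is not stated either.

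**The case against.** The best defence is that this is a journal article. It compresses reagent detail into one long sentence, lists KDR twice, and cites a method source in the section heading. A full scheme of conjugates, tubes and gates may sit in a laboratory procedure that is not shown. This stands to the extent that the failure is proved only for the panel as described, and no one can say from the article what was done at the bench. It does not remove the point. The article is not silent here: it gives a dye, or a choice of dyes, for every antibody against these markers, and what it gives conflicts with its own endpoint.

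It is also fair that the count is only part of objective (c), which covers microparticles too, and that circulating endothelial cells are identified separately by CD146.

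A reader might infer several stronger claims that the document does not support:

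- *KDR and CD133 always collide on PE.* That is the first-mentioned stain, but the same sentence also allows KDR on FITC. The collision always occurs, though not always between that pair.
- *100,000 events are too few.* This rests on an assumed frequency. At 0.1% the counting CV would be 10%.
- *Counting error would hide group differences, or the measured population would be mostly other cells.* The article gives no expected difference, between-child spread or cell frequencies from which to judge either.
- *A child's result is lost because analysis is immediate.* The statement about immediate analysis belongs to the microparticle assay. For the angiogenic cells the text describes fixation before analysis.

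**Conclusion.** The point holds as an inconsistency between the stated endpoint and the stated assay. With FITC and PE only, none of the four permitted assignments resolves cells positive for CD34, KDR and CD133, and pairwise tubes do not recover that count. The conclusion needs no outside figure. It assumes only that the two named dyes are the whole panel for this assay, as the article presents it.

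Its reach is limited to the progenitor-cell part of secondary objective (c) and any correlation that uses that count. The primary comparisons of FMD and PORH do not use it, and neither sample size calculation draws on it. It should be corrected, but it does not threaten the main result.

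The event number is not an error. It is unjustified, and would be imprecise (CV 32% or more) if target cells are 0.01% of acquired events or fewer.

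**What to change.** Either of two changes resolves the inconsistency:

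1. **Keep the three-marker definition.** Assign CD34, KDR and CD133 three separable dyes in one tube, with CD45 on a fourth if it is read in the same tube. State one dye per marker and the gating sequence. Confirm that the cytometer can read the added dyes, since the article names an instrument only for the microparticle assay.
2. **Keep two dyes and redefine the endpoint** as two-marker populations in separate tubes. For example, CD34+/KDR+ and CD34+/CD133+ are both resolvable with CD34 on FITC and the partner on PE, provided CD45-FITC is left out of those tubes. The definition and objective (c) should then name these populations.

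The first option costs different antibody conjugates. Any children already assayed with the two-dye panel as described could be reported only as two-marker populations, and only for pairs that were on different dyes without a third marker sharing either channel. The second option costs the triple-positive endpoint itself. If the laboratory already uses a fuller panel, the cost is a corrected description.

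In the same edit, say whether the 100,000 events are total or monocyte-gated, and give the expected frequency or minimum target-cell count behind that number. This needs no change to the assay unless the expected frequency proves low.
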